#### Degree of Statistical Significance

The results will be considered significant at the 5% threshold.

#### Methods for Considering Missing, Unused, or Invalid Data

No imputation of missing values will be performed.

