Initially, univariate analysis with chi-squared tests (or Fisher exact if the conditions are not met) for qualitative variables and Student two-sided *t* test (or Wilcoxon test if the conditions are not met) for quantitative variables will be performed.Subsequently, multivariate analysis with all exploratory variables with a significance threshold lower than 0.2 will be introduced into the multivariate model. The interactions between the variables will be ensured in advance. If an interaction is detected, the choice of the variable to be introduced will be made based on clinical relevance. The choice of the best multivariate model will be made using a selective downward procedure on the Akaike information criteria.Health literacy will be assessed via the score obtained by the REALM-R (a score <6 demonstrating a low health literacy score). The before/after health literacy increase will be assessed using a McNemar chi-square test using the score qualitatively (threshold at 6). A logistic regression model with random effect will be used in the multivariate analysis to eliminate any confounding factors with the same methodology as described above. The same methodology will be applied to the HAD scale (threshold at 11). The analysis of quantitative scales such as the EQ-5D-3L or the confidence level will be performed with matched (or otherwise Wilcoxon) Student tests between inclusion and M12. Random multivariate linear models will be implemented to adjust for any confounding variables. For the EQ-5D-3L, analyses of time until deterioration can be implemented if necessary.

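### With imputation ruled out, the planned inclusion-to-month-12 tests, and the PAM-13 change compared between centres, use only patients measured at month 12, in a setting where absence is plausibly related to outcome

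*Protocol article*

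**What the plan says.** Under Methods for Considering Missing, Unused, or Invalid Data, the protocol article gives a single rule: "No imputation of missing values will be performed".

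The Design section of the Statistical Analysis names the before/after tests.

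- **REALM-R:** "The before/after health literacy increase will be assessed using a McNemar chi-square test using the score qualitatively (threshold at 6"; HAD follows the same method with its own cut-off of 11.
- **EQ-5D-3L and the confidence level:** the analysis "will be performed with matched (or otherwise Wilcoxon) Student tests between inclusion and M12".
- **PAM-13:** the baseline-to-month-12 difference is to be calculated for every patient in each centre. Its mean is then compared between the centre with a nurse navigator and each of the four others.

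The same section also plans models. For the dichotomised scales, "A logistic regression model with random effect will be used in the multivariate analysis to eliminate any confounding factors". Random-effect linear models are planned for the quantitative scales, again to adjust for confounders. PAM-13 has a mixed linear model for its evolution over 12 months, and a time-to-deterioration analysis of EQ-5D-3L is optional.

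All questionnaires are scheduled at enrolment, month 6 and month 12. Oncology nurses complete them while the patient attends for intravenous chemotherapy or immunotherapy (Implementation Study; Screening and Inclusion).

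**The concern.** A paired or McNemar test has nothing to compute for a patient with only one of the two values. Once imputation is excluded, these tests describe only patients still being measured at month 12, and the month-6 scores contribute nothing.

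That would matter little if absence at month 12 were unrelated to outcome. Here it is tied to the data-collection setting: a patient no longer coming for intravenous treatment is outside the situation in which the questionnaire is filled in. Patients have any cancer, and the required life expectancy of at least one year equals the length of follow-up. Those who progress, stop treatment or die are plausibly both worse off and unmeasured. The change in quality of life and anxiety among the remaining patients would then look better than the change in the enrolled population.

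For PAM-13 the text promises a difference for all patients, which cannot be calculated where month 12 is missing. The between-centre comparison is distorted if centres differ in how many, or which, patients they lose.

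**Working it through.** **Stated figure.** The enrolment cap reproduces: 3 × 150 + 2 × 75 = 600 (Number of Subjects Needed). The article states no attrition rate, standard deviation or effect size, so everything below rests on assumed inputs.

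**Step 1: patients left for the paired tests.** Complete pairs = N × (1 − m), where m is the assumed share without month 12.

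| m | of 600 | of a 150-patient site |
|---|---|---|
| 10% | 540 | 135 |
| 20% | 480 | 120 |
| 30% | 420 | 105 |
| 40% | 360 | 90 |
| 50% | 300 | 75 |

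A 75-patient site with 30% missing keeps about 52.

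**Step 2: bias of the mean change.** The simulation used 600 patients, three visits, SD 1, correlation 0.6 between visits, true change 0, higher score better, and 60 runs per setting. Dropout at month 12 was logistic, and likelier the worse the change. The complete-pair mean was compared with the month-12 contrast from a random-intercept mixed model fitted to all available visits without imputation. Entries are bias in SD units; a positive value means the result looks too favourable.

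| Dropout depends on | Analysis | 10% | 20% | 30% | 40% |
|---|---|---|---|---|---|
| Observed change to month 6 (missing at random) | Complete pairs | +0.05 | +0.08 | +0.11 | +0.15 |
| | Mixed model | +0.01 | 0.00 | 0.00 | 0.00 |
| Unseen change to month 12 (not at random) | Complete pairs | +0.08 | +0.15 | +0.23 | +0.30 |
| | Mixed model | +0.06 | +0.10 | +0.16 | +0.21 |

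The SD of a change is √(2 × (1 − 0.6)) = 0.894, so with 420 pairs the simulation error is about 0.894/√420/√60 = 0.006. The fitted model matched the correlation pattern used to generate the data, which favours it. The figures are for a continuous score; they do not carry over directly to the dichotomised REALM-R and HAD.

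**Step 3: how much the mixed model repairs.** Under missing at random, essentially all of the bias goes. Under missing not at random with 30% missing, it removes (0.23 − 0.16)/0.23 = 30%.

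A second illustration assumes that 30% of patients decline by 1 SD at month 12 (0.6 SD at month 6) and the rest do not. Dropout for decliners and non-decliners is 20% and 5% at month 6, then 50% and 7% at month 12.

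- Completion: 0.7 × 0.95 × 0.93 + 0.3 × 0.80 × 0.50 = 0.618 + 0.120 = 0.738.
- Completers' mean change: −0.120/0.738 = −0.163 SD, against a true −0.30.
- By simulation: true −0.301, completers −0.165, likelihood analysis using month 6 −0.198. The likelihood analysis removes 0.033/0.136 = 24% of the bias.

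**Step 4: centre comparison.** The bias of a between-centre contrast is the difference of the two centres' biases. With the not-at-random figures, centres losing 30% and 10% give 0.23 − 0.08 = 0.15 SD. Centres losing the same share by the same mechanism give 0.

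**The case against.** The strongest reply is that the plan already contains the remedy. Excluding imputation does not make every analysis complete-case. The random-effect logistic and linear models, the PAM-13 mixed model and the optional time-to-deterioration analysis can all use patients without month 12, and likelihood-based models are valid under missing at random without imputation. This stands. A reader might infer that all the secondary analyses are restricted to patients with both visits; the Design section does not support that. What remains is that the random-effect models for the secondary scales are given only as confounder adjustment, with no statement that month 6 enters them, while the change itself is assigned to the paired tests.

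A reader might also extend the point to the factor search, where "The choice of the best multivariate model will be made using a selective downward procedure on the Akaike information criteria". That does not follow. Such selection needs one common set of patients with complete covariates; it does not by itself select month-12 attenders. The article lists no covariates and gives no rates of missing covariates, so any loss there is a separate question that the document does not show.

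The direction is also less certain than it first looks. Patients who finish treatment in good condition leave the same setting as those who deteriorate. Nothing in the article indicates that REALM-R, a literacy test, should worsen with progression, and the direction for PAM-13 is likewise not established. Finally, these are within-patient changes in an implementation study whose sample size answers no efficacy hypothesis, which limits the consequences.

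**Conclusion.** The point holds for the named before/after tests and for the PAM-13 difference: the rule and the tests together fix complete-pair analyses that discard month-6 data. Because measurement is tied to treatment visits, selective loss is plausible, and the likely direction for quality of life and anxiety is too favourable.

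The size cannot be derived from the document. If 30% lacked month 12, the illustration gives a bias of 0.11 SD (missing at random) to 0.23 SD (not at random). It is tempting to attach a firm figure, such as decline being understated by nearly half, as in the second illustration. That result follows from the assumed dropout of 50% against 7%, and the article supplies neither number.

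This should be changed before analysis. It does not invalidate the study, and most of the machinery is already planned.

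**What to change.** 1. For EQ-5D-3L, the confidence level, HAD and REALM-R, state that the main analysis of change is the month-12-versus-inclusion contrast from the random-effect models already planned. Fit them to all inclusion, month-6 and month-12 data with visit as a categorical term, and state the missing-at-random assumption.
2. For PAM-13, base the centre comparison on the corresponding centre-by-visit contrast from the planned mixed linear model. Drop the claim that the simple difference is available for all patients.
3. Keep the paired t, Wilcoxon and McNemar tests as supportive, labelled as complete-pair analyses, and report month-6 and month-12 completion by centre with reasons.
4. Add one missing-not-at-random sensitivity analysis, because the mixed model removes only part of the bias if dropout depends on unseen month-12 values.
5. Reword the missing-data section so that excluding imputation in the main analysis does not exclude whatever that sensitivity analysis needs.

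The cost is revised wording and a little more programming, with no new questionnaires or visits. The main downside is reliance on missing at random, which the data cannot confirm; hence item 4. Estimated changes may also look less favourable.

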### Ethical Considerations

Declarations indicating that the research will be conducted in accordance with the protocol and good practice and legislative and regulatory provisions are in force. The protocol is in accordance with the principles of ethics established by the 18th World Medical Assembly (Helsinki 1964) and the amendments established at the 29th (Tokyo 1975), 35th (Venice 1983), 41st (Hong Kong 1989), 48th (Somerset West 1996), 52nd (Edinburg 2000), 54th (Washington 2002), and 59th World Medical Assembly (Seoul 2008) and reviewed at the 64th World Medical Assembly (Fortaleza 2013). The protocol will be conducted in accordance with the International Conference of Harmonization guidelines of Good Clinical Practice.

## Discussion

The purpose of this project is to implement the PAM-13 within oncology nursing practices at 5 comprehensive cancer centers. To our knowledge, no measurement of patient activation has been used in routine practice or has been experimented in cancerology in France. Analyzing the impact of nursing intervention through such a measure, depending on the type of facility, could lead to strengthening some of them, modifying care practices, and enabling better patient management. In the end, this evaluation via the PAM-13 should allow for a greater understanding of the contribution of these specific nursing interventions of care, the objective being to confirm better activation of the patient in establishments that use a combined set of measures.

The use of an activation measure would constitute a major change in the management of patients with cancer. As the patient’s activation is evolutive, the implementation of targeted nursing interventions would increase the activation. A number of programs have demonstrated their ability to increase the level of patient activation [85-87]. They generally focus on the acquisition of new skills by patients and support a sense of ownership of their health. These different research studies showed that peer support, changes in the patient’s social environment, coaching, and health education courses have been deemed valuable [85-87]. Furthermore, measuring the level of activation and the implementation of measures intended to increase the level of activation would constitute a significant advantage in reducing social health inequalities [88]. Indeed, different studies having implemented this type of intervention have shown that the patients who experience the lowest activation levels are those who tend to show the greatest increase in the activation level [46]. This may be partially due to a “ceiling” effect; not much improvement can be made in patients who already demonstrate high levels of activation. However, this also shows that effective interventions can help disengaged patients become proactive toward their health [85,89,90].

Finally, we assume that studying the implementation of a tool for measuring the degree of activation of the patient of nursing practices in oncology would enable a dynamic evaluation of changes in the patient’s cancer care pathway in order to optimize the latter. The implementation methodology using the RE-AIM evaluation framework would specify the real-life efficiency of the PAM-13, the different adaptations of the centers that have implemented it routinely, the key success factors and pitfalls to avoid, and the various parameters impacting its efficiency [66]. Due to the study and its resulting detailed and analytical description of the contents of the use of the PAM-13 in the comprehensive cancer center concerned, we will produce recommendations for the dissemination of such an intervention in order to manage the deployment of an activation measurement for all new patients with cancer at any requesting facility.

In conclusion, this study of implementation conducted at 5 French comprehensive cancer centers could help define a new strategy for sustaining patients’ empowerment in the cancer care pathway. The use of a PAM would constitute a notable change in the management of patients with cancer. Systematic integration of the measure should make it possible to implement targeted oncology nursing interventions, strengthening some of them in order to offer patients a personalized cancer care pathway adapted to their needs. Indeed, with the arrival of immunotherapy combinations, it appears essential to focus on patients’ empowerment in the management of their medical care. Moreover, the measurement of the level of activation and the implementation of measures to strengthen such activation would constitute a significant advantage in reducing social health inequalities.

## Appendix

Multimedia Appendix 1 Overview of the implementation outcomes from the RE-AIM (Reach, Effectiveness, Adoption, Implementation, and Maintenance) framework.

Multimedia Appendix 2 SPIRIT checklist.

Multimedia Appendix 3 Peer-review reports from DGOS-France, translated in English.

## Abbreviations

COM-B: Capability, Opportunity, Motivation, and Behavior
EQ-5D-3L: European Quality of Life-5 Dimensions-3 Level
HAD: Hospital Anxiety and Depression
PAM-13: Patient Activation Measure-13 item
PARACT: PARAmedical Interventions on Patient ACTivation
RE-AIM: Reach, Effectiveness, Adoption, Implementation, and Maintenance
REALM-R: rapid estimate of adult literacy in medicine-revised
TDF: Theoretical Domains Framework
